Mepilex Ag® is a silver sulfate soft silicone foam dressing that allows for continuous silver delivery to the wound, good exudate management, provides a moist environment and thermal insulation making this dressing ideal for partial thickness burns [25]. In a randomised trial of children (*n* = 96) with partial thickness burns, silver-impregnated foam dressings were effective in shortening the TTRE and reduced pain during dressing changes [9]. Despite this, silver impregnated dressings are more expensive per dressing change when compared to Biobrane® and a Regenerative Epithelial Suspension (RES™) [10], require frequent dressing changes due to non-transparent design and are associate with adverse effects such as cytotoxicity and argyria. Over the last 30 years, epithelial suspension preparation for burn wound management has undergone a multitude of transformations including the number of enzymatic degradation agents used, co-delivery systems with various cell carriers and a range of preparation times (few weeks to under an hour) [7, 26]. The RECELL® Autologous Cell Harvesting (ACH) device (Avita Medical, California, USA) was first introduced almost two decades ago [27]. In approximately 30 min, a Regenerative Epithelial Suspension (RES™) containing basal keratinocytes, melanocytes, fibroblasts, melanocytes, Langerhans cells and epidermal basal cells [28] is obtained from a donor skin sample as small as 1 cm^2^. The faster preparation allows for a readily available suspension compared to the cultured keratinocytes, where wait times can be a few weeks.

Few studies have comprehensively assessed the effectiveness of the RES™ in the management of childhood burn injuries. Most of the published literature is based on the adult cohort and there is a paucity of data based on the paediatric population. When compared to standard care, wounds treated with RES™ had longer operative times [29], more wound infection [10] and once applied the RES™ requires a retention dressing such as Biobrane®, to keep *in situ* [10]. However, in the other studies, application of RES™ was associated with less post-operative pain [10, 29], smaller donor site area [29, 30], shorter TTRE [10, 29, 30], fewer dressing changes and cost-effectiveness [10, 31]. Autologous skin cell suspensions show promising potential to change current burn wound management approaches from dressing based to cell-based therapy.

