First introduced in 1979 [11], Biobrane® (Smith and Nephew, Hull, UK) is a composite biosynthetic skin substitute composed a matrix of short porcine collagen peptides bonded to a layer of nylon that is enveloped in silicone [8]. The benefits of using Biobrane® include shorter TTRE, improved mobility, shorter hospital stay, ease of application, ability to visualise the wound [32] and reduced pain [10–12, 33, 34]. For clean wounds, this transparent dressing is able to stay *in situ* for up to 14 days, thus supporting the cost-effective treatment of burn injuries [35]. Failure of Biobrane® to adhere to the wound bed occurs once counts exceed 10^5^ organisms/gram of tissue [36]. Reported infection rates associated with Biobrane® range from 5 to 22% [12, 37, 38]. However, Lal. et al. demonstrated that infection rate upon application of Biobrane® to superficial partial thickness scald burns in children with 48 h of injury did not differ when compared to a topical silver dressing [39]. Biobrane® recreates the barrier function of the skin and has been used as a dermal salvage option for burn wounds over the last four decades.

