### Monitoring

Minimal adverse events are expected from the proposed interventions. At the study centre, known potential adverse events (e.g. infection, haematoma, intensive care admissions) have a standardised management protocol. Adverse events related to the interventions will be monitored through review of patient medical records, by guardian and participant (where applicable) self-report and by the treating clinicians. All adverse events will be communicated to the clinical health service and Human Research Ethics Committee (HREC). Discontinuation or alteration of treatment will be at the discretion of the treating clinical team. An independent Safety Monitoring Group will also monitor all aspects of patient safety throughout the study on a regular basis. An interim analysis will be completed by an independent statistician, who will be blinded to the treatment allocation after a minimum of 30 participants have been recruited.

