### Randomisation and allocation

To reduce the chance of prediction of treatment allocation, a procedure which randomly allocates participants in groups using a random step size will be used [77]. The randomisation sequence will then be uploaded into Research Electronic Data Capture (REDCap) randomisation module [78] by a third party person not associated with the study. Upon obtaining informed consent for the participation, baseline data (participant demographics including Fitzpatrick Skin Type, burn injury time, depth, TBSAB, injury mechanism and history of first aid prior to enrollment) will be collected. An investigator aligned with the study will complete the randomisation using REDCap and inform the treating clinicians of the allocated intervention group.

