### Statistical analysis

In the exploratory stage, data will be graphed, and summary statistics will be calculated for all outcomes. Data will be analysed using the ‘Intention to Treat’ principle. The primary outcome data will use the survival analysis model (both Kaplan-Meier analysis and Cox proportional hazards regression), with the time to healing as the main outcome and dressing group as the explanatory variable. All other data will be analysed using appropriate methods for longitudinal data such as mixed model’s regression analysis or generalised estimating equations (GEE). A GEE is better suited for estimating population average effects whereas mixed models are better suited for understanding the source of correlation and its structure. Thus, they are complementary ways of analysing the data rather than opposing. It should also be noted that for symmetrical outcome variable distributions (such as normally distributed) both methods should give similar results. Statistical significance will be set at *p* < 0.05. The data set will be analysed with SPSS (IBM Corporation, Armonk, NY, USA) and Stata (StataCorp, College Station, TX, USA) software where appropriate.

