Based on past trials and studies at the study site, a limitation of this study is the anticipated large dropout rate. Potential attrition bias will be addressed by examining whether the extent and reasons for dropout are balanced across the groups [83]. Although different dropout rates across the three groups are not anticipated, a sensitivity analysis will be run to check for any differences. It is expected that random drop out will result in larger confidence intervals but not bias. In addition, if there is no imbalance, then attrition bias is not likely to be a problem [83]. Limitations associated with burn depth assessment and wound infection diagnosis will be adjusted for during statistical analysis. The BRACS randomised trial will add new knowledge regarding the comparative effectiveness of autologous skin cell suspension for the management of partial thickness and paediatric burn injuries.

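### The Discussion promises adjustment for wound infection, which arises after randomisation, while the primary Cox model names dressing group only: reconcile the two and keep infection out of the primary comparison

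*Protocol article*

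**What the plan says.** Two places in the protocol article bear on what the primary analysis adjusts for.

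- **Statistical analysis.** The data are analysed under the "Intention to Treat" principle. The primary outcome, time to re-epithelialisation (TTRE), is analysed by Kaplan-Meier and Cox regression "with the time to healing as the main outcome and dressing group as the explanatory variable". No other covariate is named.
- **Discussion, limitations paragraph.** "Limitations associated with burn depth assessment and wound infection diagnosis will be adjusted for during statistical analysis". The sentence does not name the analysis, the variable or the method.

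Other sections say what kind of variables these are.

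- **Monitoring** treats infection as an adverse event: "known potential adverse events (e.g. infection, haematoma, intensive care admissions) have a standardised management protocol".
- **Background** cites one study with "more wound infection" under the cell suspension than under standard care. It reports Biobrane infection rates that "range from 5 to 22" per cent. It also cites a study of superficial partial thickness scalds in children in which Biobrane and a topical silver dressing did not differ in infection.
- **Discussion** says that introduced pathogens would delay TTRE.
- **Randomisation and allocation** lists the baseline data, including "burn injury time, depth, TBSAB, injury mechanism and history of first aid prior to enrollment", collected after consent and before the allocation step.
- **Background** calls the association between burn depth and TTRE established.
- **Operative procedures** makes the surgeon's depth assessment primary, and places the laser Doppler depth measurement after randomisation.

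**The concern.** A covariate in the primary model of a randomised comparison should be fixed before treatment can act on it. Wound infection is not. It arises after the dressing is applied, it may depend on which dressing was applied, and it slows healing. That makes it a plausible mediator of the effect the trial sets out to measure. Group A's dressings are described as antimicrobial, so preventing infection is part of how they are meant to work. A model that holds infection constant gives silver no credit for that, and excuses the other two arms any delay caused by infection.

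Participants would still be analysed in their randomised groups. The quantity estimated would change, from the total effect of the dressing to an effect with the infection route removed.

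The unrestricted Discussion sentence also leaves open, after the data are seen, whether infection enters the primary model. That choice could alter the main conclusion.

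**Working it through.** **Step 1. The plan's own figure.** The claim concerns model specification, and no stated number tests it. The only related figure is the sample size. With 25 per group and 10% attrition, 25 / 0.9 = 27.8, rounded up to 28, and 3 × 28 = 84, which matches. The power step cannot be reproduced because no median, hazard ratio (HR) or event proportion is given. Solving back for one pairwise two-sided logrank test with 50 healed at 80% power gives HR = exp[(1.960 + 0.842) / √(50 × 0.25)] = 2.21. That value is used below as an assumed direct effect.

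**Step 2. Side by side.** If the Statistical analysis section governs, neither depth nor infection is in the primary model. If the Discussion sentence governs all analyses, both are. The text does not say which, so the supportable finding is a conflict.

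**Step 3. What adjusting for infection would do (illustration).** All of these inputs are assumptions: infection 5% in one arm and 22% in the other (the two ends of the Biobrane range, assigned to arms for illustration), HR 0.4 for mid-dermal depth, infection treated as a fixed yes/no indicator, Weibull times with shape 3, no censoring, and 50,000 per arm.

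| Direct dressing HR | HR of infection on healing | HR adjusted for depth (total effect) | HR adjusted for depth and infection |
|---|---|---|---|
| 1.00 | 0.6 | 0.90 | 1.00 |
| 1.00 | 0.4 | 0.83 | 0.99 |
| 1.00 | 0.25 | 0.77 | 1.00 |
| 2.21 | 0.6 | 1.96 | 2.21 |
| 2.21 | 0.4 | 1.72 | 2.20 |
| 2.21 | 0.25 | 1.45 | 2.20 |

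A hand check of the second row, within a depth stratum: at the start the hazard ratio is (0.78 + 0.22 × 0.4) / (0.95 + 0.05 × 0.4) = 0.868 / 0.970 = 0.89. At cumulative hazard 1 for an uninfected wound, the hazards are (0.2870 + 0.4 × 0.1475) / 0.4344 = 0.796 and (0.3495 + 0.4 × 0.0335) / 0.3830 = 0.948, with ratio 0.84. At cumulative hazard 2 the same formula gives 0.710 / 0.911 = 0.78. An average near 0.83 fits.

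Adding an unmeasured cause of both infection and slow healing (assumed HR 0.5 on healing, odds ratio 3 for infection) puts the infection-adjusted HR at 1.03 to 1.04 when there is no direct effect. Collider bias is therefore small here, and the removal of the mediated effect is the main issue.

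If infection is equally frequent in both arms and there is no direct effect, the arms have the same healing distribution, and the HR is 1 with or without the adjustment.

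**Step 4. What baseline depth would add (illustration).** 25 v 25, assumed conditional HR 2.21, 3,000 simulated trials per setting.

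| Depth HR | Power, unadjusted | Power, depth-adjusted | Median HR, unadjusted | Median HR, adjusted |
|---|---|---|---|---|
| 0.5 | 68.6% | 74.9% | 2.07 | 2.26 |
| 0.4 | 65.3% | 75.0% | 2.03 | 2.27 |
| 0.3 | 57.6% | 75.7% | 1.91 | 2.28 |

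The differences are about 6, 10 and 18 points. With no dressing effect, the unadjusted model rejects in 5.2% to 6.0% of trials and the adjusted model in 5.7% to 6.2%, so leaving depth out does not make the test invalid. The low unadjusted power depends on treating 2.21 as the conditional effect. If 2.21 were the marginal effect, unadjusted power would be about the design's 80% by the formula.

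**The case against.** The strongest reply is that the Discussion sentence is read for more than it says. It sits in a limitations paragraph and never mentions the Cox model. Limitations of infection diagnosis could mean diagnostic misclassification handled in a sensitivity analysis. This stands: a reader might infer that the primary model will condition on infection, but the documents do not say so.

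Three other inferences are tempting and not supported.

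- **That the plan leaves out depth.** The same sentence names burn depth assessment. One cannot use the Discussion to put infection in and the Statistical analysis section to take depth out. A fuller covariate list may also sit in an analysis plan that is not shown.
- **That infection is an established effect of the dressings.** The excess with the suspension rests on one citation. The range of 5 to 22% describes different reports on one product and is not a contrast between arms. One cited paediatric study found no difference between Biobrane and silver, though it covers superficial partial thickness scalds and neither the suspension nor mid-dermal burns.
- **That an unadjusted Cox model is an error.** It is a valid randomised comparison. Its HR lies nearer 1 because it estimates a marginal rather than a conditional effect. No section shows TBSAB to be a strong predictor of TTRE.

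What survives is the conflict between the two sections, and the fact that one reading of it would put a post-randomisation variable into the primary comparison.

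**Conclusion.** The concern holds in a limited form. The Statistical analysis and Discussion sections disagree on adjustment, and adjusting the primary TTRE comparison for infection would remove any infection-mediated part of the dressing effect.

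Under the assumed values, total-effect HRs of 0.77 to 0.90 move to about 1.00, and HRs of 1.45 to 1.96 move to about 2.20. These figures show direction and possible scale only. They rest on an assumed 5% v 22% split and assumed HRs for infection and depth. If the arms have similar infection rates, the distortion largely goes away.

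The depth half is a precision gain of roughly 6 to 18 power points under assumed depth effects, conditional on the reading of HR 2.21 given above. It does not correct an error.

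**What to change.** 1. In the Statistical analysis section, state that wound infection is not a covariate in the primary TTRE analysis. Amend the Discussion sentence to match, saying whether it meant diagnostic error and in which analysis.
2. Report infection by arm as a safety outcome. Label any infection-adjusted model as exploratory.
3. Prespecify the primary Cox model as dressing group plus surgeon-assessed depth recorded before randomisation, optionally with TBSAB, and show the unadjusted result alongside.
4. Do not use laser Doppler depth as a baseline covariate unless it is confirmed to precede application of the dressing, since it is measured after randomisation.

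The cost is wording only. Depth and TBSAB are already collected before allocation, infection is already monitored as an adverse event, and the sample size does not change.

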## Trial status

Recruitment started in May 2018 and will proceed for a period of 18 months. Follow-up consultations will be in the outpatient setting at the 3, 6 and 12-month post-date of burn injury. Intended completion of the study is December 2020.

## Data Availability

Not applicable

## Abbreviations

2D: Two-dimensional
3D: Three-dimensional
ACH: Autologous cell harvesting
ASCS: Autologous skin cell suspension
BBSIP: Brisbane Burn Scar Impact Profile
BRACS: Biobrane®, RECELL® Autologous skin Cell suspension and Silver dressings
CHU9D: Child Health Utility 9D
COD: Change of dressing
DOI: Date of injury
FLACC: Face, Legs, Activity, Cry, Consolability
FPS-R: Faces Pain Scale-Revised
GEE: Generalised Estimating Equations
HREC: Human Research Ethics Committee
HRQOL: Health-related quality of life
ICC: Intraclass correlation coefficient
LDI: Laser Doppler Imaging
NRS-I Proxy: Numeric Rating Scale–Itch Proxy
NRS-I: Numeric Rating Scale–Itch
NRS-P Proxy: Numeric Rating Scale–Pain Proxy
NRS-P: Numeric Rating Scale–Pain
OPD: Outpatient department
POSAS: Patient and Observer Scar Assessment Scale
QLD: Queensland
QUT: Queensland University of Technology
REDCap: Research electronic data capture
RES™: Regenerative Epithelial Suspension
SPIRIT: Standard Protocol Items Recommendations for Interventional Trials
SSA: Site-specific approval
TBSAB: Total body surface area burned
TTRE: Time to re-epithelialisation
